### Power analysis

This cRCT has three unit levels: the municipality, healthcare facility and the individual. A simulation-based power analysis was done in SAS software 9.4 (SAS Inc., Cary, NC, USA) using the generalised linear mixed model and taking these levels into consideration (Table 6 in Appendix 3). The power analysis was used to estimate the sample size needed to detect a 10% (25% in the intervention arm and 15% in the control arm) increase in the rate of CoC completion significant at 5% and assuming a 20% dropout rate. The intracluster correlation coefficients (ICC) used in this simulation-based power analysis were 0.010, 0.015 and 0.020 [21]; and assuming that the number of participants was 5000, 7500 and 10,000, the power ranged from 0.560 to 0.828. We also confirmed in the simulation that type 1 error does not inflate. On the basis of these calculations, we aim to recruit at least 10,000 participants. The target sample size in each municipality will vary depending on the population size.

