### Randomisation and allocation concealment

This study is a two-arm study comprising an intervention arm and a control arm. The unit of randomisation in this trial is the municipality (cluster). Cluster randomisation was chosen due to the nature of the intervention and to minimise logistical and scientific difficulties associated with individual randomisation in large-scale longitudinal studies—such as contamination. Benguela Province consists of 10 municipalities of varying sizes—Baia Farta, Balombo, Benguela, Bocoio, Caimbambo, Catumbela, Chongoroi, Cubal, Ganda and Lobito. All 10 municipalities will be included in the study. Population size and basic characteristics of each of the 10 municipalities were taken into consideration during the randomisation process to ensure a balance of socio-demographic characteristics between both arms.

Municipalities were allocated to either intervention or control arms using block randomisation [22, 23] by an experienced statistician in two steps. To ensure a balance between the two study arms, we ordered the municipalities by population size then applied block randomisation as described by Gattellari et al. [24]. First, municipalities were sorted by size based on the 2014 population data provided by the National Institute of Statistics [25]. Using the data, five blocks comprising of two municipalities each were created in the order of population size. Second, municipalities were randomly allocated either to the intervention or to the control arm within each block using computer-generated results. In this step, a pair of 4-digit code assigned to each block was fed into a SAS program that automatically returned a response, assigning one of the municipalities in the block to the intervention or control arm. The statistician was unable to predict assignment to either study arm. Municipalities allocated to the intervention or control arms were revealed simultaneously to the study team and municipal authorities at the kick-off meeting marking the start of the trial.

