### Statistical analysis

The intervention arm (MCH handbook) will be compared to the control (traditional use of two stand-alone HBRs) in the main analysis. We will conduct descriptive analysis, and baseline data from the intervention and control arms will be analysed for comparability of baseline characteristics. Rates of missing data for each variable will be determined to assess the differences between the arms, and overall losses to follow-up will be determined. We will report reasons for losses within each arm and compare the reasons qualitatively.

We plan to measure intervention impact using two analysis sets: the intention-to-treat (ITT) set and the per-protocol analysis set (PPS). The ITT population will include all participants within the randomised municipalities analysed according to the municipality where they were first registered to receive MNCH services (i.e. discounting where they received second, third or fourth MNCH services) [33, 34]. The ITT population will be the primary analysis set, and all analyses will be conducted using this population unless otherwise stated. In the PPS, participant data will be analysed according to the treatment they actually received. Data from the participant with more than one MCNH service utilisation in the control arm will be included in the control arm regardless of the municipality of first registration for MNCH services in the PPS analysis.

The primary endpoint in this impact evaluation study is to compare the proportion of CoC completion achieved among mothers who received the MCH handbook in the intervention arm and those who received the traditional stand-alone HBRs in the control arm. We will evaluate the effect of the provision of MCH handbooks on CoC completion at the municipality level using a generalised linear mixed model (GLMM) assuming logit link and binomial distribution. All analyses will be based on complete case analysis. Regarding the number of healthcare service utilisations, the analysis will be conducted using survival analysis. We will also evaluate the intervention effects in a subgroup of participants based on socio-economic status, urban/rural residence and other baseline characteristics while accounting for cluster effect.

All analyses will be done using STATA (version 13 or higher, Stata Press, College Station, TX).

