## Data Availability

There are no data available in this article as no datasets were generated or analysed during the study protocol. The full datasets will be available (upon request) after they have been analysed and published.

## Appendix 3

**Table 6 Tab6:** Sample size simulation

Power		Intervention, 25%; control, 15%		
Simulation: 1000 times *α*=0.05, two-sided		Total *N*		
		5000	7500	10,000
ICC	0.010	0.776	0.808	0.828
	0.015	0.639	0.658	0.674
	0.020	0.560	0.570	0.605

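### With ten municipalities, the logit GLMM has no stated small-sample reference: an ordinary Wald z test would run at about 11-13%, and the SAS assurance on type 1 error cannot be assumed to cover it

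*Protocol article*

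**What the plan says.** Under Randomisation and allocation concealment: "The unit of randomisation in this trial is the municipality (cluster"). The ten municipalities were sorted by size, and "five blocks comprising of two municipalities each were created in the order of population size", one municipality of each pair going to each arm. The trial therefore has five clusters per arm.

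Under Statistical analysis, the effect on continuum-of-care (CoC) completion is to be evaluated at municipality level "using a generalised linear mixed model (GLMM) assuming logit link and binomial distribution". The same section says "All analyses will be done using STATA (version 13 or higher, Stata Press, College Station, TX"). It names no estimation method, no choice between Wald and likelihood ratio, no denominator degrees of freedom and no small-cluster correction. It does not rule out a correction either.

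Under Power analysis: "A simulation-based power analysis was done in SAS software 9.4 (SAS Inc., Cary, NC, USA) using the generalised linear mixed model", with three levels (municipality, facility, individual). The reader is then told: "We also confirmed in the simulation that type 1 error does not inflate". No rejection rate, test statistic or reference distribution accompanies this. Appendix 3, Table 6 ("Simulation: 1000 times", two-sided 5%) gives power from 0.560 to 0.828.

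**The concern.** The treatment effect is a contrast between five and five municipalities. However many women are recruited, about 8 degrees of freedom inform the between-municipality variance. Large-sample inference goes wrong here in two ways. Maximum likelihood divides by 10 where an unbiased estimate divides by 8, so the standard error is too small. A normal reference then ignores the uncertainty in that variance. Both make the p-value too small and the confidence interval too narrow.

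The protocol offers one reassurance, the simulated absence of inflation. It was obtained in a different package from the one fixed for the analysis, with a test that is not named. If the simulated test used a small-sample reference and the final one does not, the reassurance does not apply. The result is meant to inform a decision on nationwide scale-up, so a false-positive rate of about twice the nominal level on the single primary comparison would matter.

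**Working it through.** **Inputs from the protocol.** 10 municipalities, 5 per arm; 25% v 15%; ICC 0.010, 0.015, 0.020; N = 5,000, 7,500, 10,000; 20% dropout; two-sided 5%; 1,000 simulations. The scale and level of the ICC, the facility-level variance and the cluster sizes are not given. Assumptions: proportion-scale ICC at municipality level and, for the closed forms, equal clusters.

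**1. The plan's own figures.** With m women per municipality,

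Var(difference) = Σ over arms of p(1−p)[ICC + (1−ICC)/m]/5.

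For ICC 0.010, N=10,000, no dropout (m = 1,000): p(1−p) is 0.1875 and 0.1275, sum 0.315. The variance is 0.315 × (0.010 + 0.990/1,000)/5 = 0.000692, SE 0.0263, and effect/SE = 0.10/0.0263 = 3.80. Power against three references:

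| ICC | N | Stated | Normal | t(8) | t(4) |
|---|---|---|---|---|---|
| 0.010 | 5,000 | 0.776 | 0.954 | 0.889 | 0.775 |
| 0.010 | 7,500 | 0.808 | 0.963 | 0.905 | 0.797 |
| 0.010 | 10,000 | 0.828 | 0.967 | 0.913 | 0.808 |
| 0.015 | 5,000 | 0.639 | 0.864 | 0.764 | 0.635 |
| 0.015 | 7,500 | 0.658 | 0.877 | 0.780 | 0.651 |
| 0.015 | 10,000 | 0.674 | 0.883 | 0.788 | 0.660 |
| 0.020 | 5,000 | 0.560 | 0.767 | 0.655 | 0.532 |
| 0.020 | 7,500 | 0.570 | 0.779 | 0.668 | 0.543 |
| 0.020 | 10,000 | 0.605 | 0.785 | 0.675 | 0.550 |

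The normal reference exceeds the stated power by 14 to 22 points in every cell, and t(8) by 7 to 13 points. The t(4) values are nearer (6 of 9 cells within 2 points) but below the stated power in every cell, by up to 5.5 points. Applying 20% dropout changes little: the normal reference at ICC 0.010, N=10,000 becomes 0.964. Simulated power of the ML Wald z test was 0.977 at ICC 0.010 and 0.830 at ICC 0.020. The Monte Carlo standard error of the stated powers is about 1.2 points at 0.828 and 1.5 points at 0.605. Table 6 is therefore not reproduced as a whole under these assumptions.

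**2. Type I error in closed form.**
- z with the ML variance: reject when |t₈| > 1.96 × √(8/10) = 1.753, so P = 0.118.
- z with an unbiased variance: P(|t₈| > 1.96) = 0.086.

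**3. Type I error by simulation.** Ten clusters under the null, 2,000 replicates per scenario (standard error about 0.7 points). A random-intercept logit was fitted by maximum likelihood with adaptive quadrature. Scenarios covered ICC 0.010 to 0.020, equal and unequal clusters, 8,000 and 10,000 women, and an added facility level.

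| Test, nominal 5% | Rejection under the null |
|---|---|
| ML GLMM, Wald z | 10.9% to 12.8% |
| ML GLMM, likelihood ratio | 7.9% to 9.5% |
| ML GLMM, Wald referred to t(8) | 6.6% to 7.8% |
| Municipality-level t, 8 df | 4.3% to 5.5% |
| Paired municipality-level t, 4 df | 4.0% to 5.6% |

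A separate set (1,500 runs each, 8,000 women, 15% in both arms, sizes proportional to the Table 1 facility counts) gave 10.9%, 11.1%, 10.6% and 11.1% for Wald z at ICC 0.01, 0.02, 0.05 and 0.10, and 4.1% to 5.3% for the 8-df t test. The inflation comes from the number of clusters and hardly depends on the ICC.

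**The case against.** The strongest reply is that the protocol does not say large-sample inference will be used. Naming Stata and a GLMM fixes neither the Wald statistic nor the normal reference, a municipality-level t test can be run in Stata, and such detail is often left to an analysis plan, which is not shown here. This stands. A reader might infer that the primary analysis has an 11% type I error, or that the authors have chosen to use no small-sample degrees of freedom. The document supports neither; the 11-13% is conditional on one choice of test.

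A second reply concerns Table 6. A reader might infer that it cannot come from a z test, or that it reflects a paired analysis on 4 df. Neither follows. The simulation had three levels, and the ICC's scale and level, the facility variance and the cluster sizes are unstated. A z reference would match all nine cells if the variance were 1.5 to 1.7 times that assumed here. For example, at ICC 0.010 and N=10,000 with dropout, power 0.828 needs effect/SE of about 2.91 against 3.76, a variance ratio of (3.76/2.91)² ≈ 1.67. The 4-df values also miss in one direction throughout. Failure to reproduce the table does not show an error in it.

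Third, the authors did consider type 1 error, and using one package for design and another for analysis is no contradiction. That is fair. But the document gives a positive assurance without naming the test it belongs to, and its own power figures do not resemble a large-sample test under the plainest reading of the ICC. Whether the check transfers is unconfirmed, not refuted.

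**Conclusion.** The point holds in conditional form. With ten municipalities and the model as stated, a maximum-likelihood Wald z test rejects a true null about 11-13% of the time at nominal 5%. A likelihood ratio test (about 8-9%) and ML Wald on t(8) (about 7-8%) are also above nominal, whereas a municipality-level t test on 8 df holds about 5%. The statement that type 1 error does not inflate cannot be assumed to cover the Stata analysis until it is shown to refer to the same test.

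The type I figures rest on five clusters per arm and on simulation over the scenarios listed. The comparison with Table 6 rests on proportion-scale municipality-level ICCs and is supporting evidence only: it does not show which model produced the table or that the table is wrong.

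**What to change.** Name a primary test that holds its level with ten clusters. Two options:

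- analyse municipality-level proportions or log-odds with t on 8 df (7 if one cluster-level covariate is added), which can be run in Stata; or
- keep the GLMM with a small-sample degrees-of-freedom correction, after checking its type I error by simulation. No such correction was tested above, and simply referring the ML Wald statistic to t(8) still gave 6.6% to 7.8%.

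A within-block permutation test should not be the primary test at 5%: with five pairs, its smallest two-sided p-value is 2/2⁵ = 2/32 = 0.0625.

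Then rerun Table 6 and the type I error check with that exact test, stating the ICC scale and level and the facility variance, and report both power and rejection rate under the null.

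The cost is a wording change and a rerun of the simulation. Confidence intervals will be wider than under a large-sample test, and the stated power may change.

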**Primary outcome**				
Complete CoC (maternal behaviour-based)	Time-dependent composite outcome. Complete CoC is the minimum number of ANC visits + facility-based delivery + PNC for mother and newborn + child vaccinations at two time points—at birth and at 2~3 months. Includes women who attended ANC and other MCNH services only. Complete CoC = 1 when all indicators = 1	Binary	First ANC timing	Timeline divided into ≤ 20, 21~30, 31~37 and 38 weeks~ ga
			No. of ANC services	< 4 = 0, ≥ 4 = 1 (≤ 20 weeks); < 3 = 0, ≥ 3 = 1 (21–30 weeks); < 2 = 0, ≥ 2 = 1 (31~37 weeks); < 1 = 0, ≥ 1 = 1 (38 weeks)
			Facility delivery	No = 0; yes = 1
			PNC_mother	No HBR record = 0; HBR record = 1
			PNC_child	No HBR record = 0; HBR record = 1
			Vaccinations at birth and at 2 months infant age	< 2 vacc clinic visits = 0; 2 vacc visits = 1

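### The protocol makes an ITT set of all registered women primary but fixes complete case for every analysis, so about a fifth of that set is expected to be left out with no alternative analysis, which can bias the CoC effect

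*Protocol article*

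**What the plan says.** All references are to the protocol article.

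- **Population (Statistical analysis).** "The ITT population will include all participants within the randomised municipalities analysed according to the municipality where they were first registered". Also: "The ITT population will be the primary analysis set, and all analyses will be conducted using this population unless otherwise stated".
- **Missing data (Statistical analysis).** "All analyses will be based on complete case analysis". No exception is given.
- **Expected loss (Power analysis).** The sample size was set "assuming a 20% dropout rate", with a recruitment target of at least 10,000.
- **Primary outcome (Table 4).** "Complete CoC = 1 when all indicators = 1". The components are ANC visits, facility delivery, postnatal care for mother and for child, and two vaccination visits.
- **Planned handling of losses (Statistical analysis; Losses to follow-up).** Missing-data rates, the proportion lost and the reasons for loss are to be compared between arms. Nothing is said to follow if they differ.
- **Data on the women who are lost (Table 3).** The baseline survey collects socio-demographic, household, pregnancy-history, health-behaviour and ANC data. Delivery, postnatal and vaccination data come from the single visit at 3 months postpartum.

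**The concern.** The two rules describe different populations. An ITT set of all registered women includes those not found at 3 months; a complete-case analysis excludes them. The protocol itself fixes the method for every analysis, so this is not a detail left open for a statistical analysis plan.

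Loss is unlikely to be unrelated to the outcome. CoC completion measures continued contact with facilities, and a woman who drifts away from care may also be harder to find at home at 3 months. Neither participants nor trial personnel are blinded (Blinding section), and only one arm receives the handbook, the handbook training and community mobilisation (Table 2). Who is lost could therefore differ between the arms. If so, the estimated effect can shift in either direction, and the plan as written provides no second analysis to show it.

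A smaller gap concerns partly observed composites. CoC requires every component to succeed, so one definite failure settles it at 0. The protocol does not say that a woman with such a failure is kept as 0 when another component is missing.

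**Working it through.** **Inputs from the protocol.** Dropout 20%; recruitment target 10,000; target effect "detect a 10% (25% in the intervention arm and 15% in the control arm) increase in the rate of CoC completion". Only an overall dropout figure is given. Every split by arm, and every CoC rate among the lost, is an assumption. Clustering is ignored because the question is bias, not precision. The power figures in Table 6 do not enter.

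**1. Size of the omission.** 0.20 × 10,000 = 2,000 women.

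**2. The target on the odds-ratio scale** (the planned model has a logit link). (0.25/0.75) / (0.15/0.85) = 1.89.

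**3. When complete case biases the comparison.** Let p be true CoC in an arm, and l1 and l0 the loss among completers and non-completers. Then

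P(CoC = 1 | observed) = p(1 − l1) / [p(1 − l1) + (1 − p)(1 − l0)].

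The observed odds are the true odds times (1 − l1)/(1 − l0). The odds ratio is unchanged whenever that factor is equal in the two arms. Taking the truth as 25% v 15%:

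| Assumed loss (intervention / control) | Complete cases show | RD, points | OR |
|---|---|---|---|
| 15% / 25%, unrelated to CoC within arm | 25.0% v 15.0% | 10.0 | 1.89 |
| 10% of completers and 22% of non-completers, same in both arms | 27.8% v 16.9% | 10.9 | 1.89 |
| Total 25% / 15%, with 10% of completers lost in each arm | 30.0% v 15.9% | 14.1 | 2.27 |
| Total 15% / 25%, with 10% of completers lost in each arm | 26.5% v 18.0% | 8.5 | 1.64 |

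Third row: 0.25 × 0.90/0.75 = 0.300 and 0.15 × 0.90/0.85 = 0.159. Fourth row: 0.25 × 0.90/0.85 = 0.265 and 0.15 × 0.90/0.75 = 0.180.

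**4. Illustration with no true effect.** Assume true CoC of 15% in both arms and 5% among the lost, with loss of 15% in the intervention arm and 25% in the control arm.

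- Intervention: (0.15 − 0.15 × 0.05)/0.85 = 0.1425/0.85 = 16.8%
- Control: (0.15 − 0.25 × 0.05)/0.75 = 0.1375/0.75 = 18.3%

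The spurious difference is −1.6 points. At 10% v 30% loss the figures are 0.145/0.90 = 16.1% and 0.135/0.70 = 19.3%, a difference of −3.2 points. Reversing the split reverses the sign.

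**5. What complete cases alone leave open.** Suppose complete cases show exactly 25% v 15%, with 20% lost in each arm.

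- Missing counted as not complete: 0.80 × 25% = 20% v 0.80 × 15% = 12%; RD +8 points, OR 1.83.
- Worst case (all lost fail in the intervention arm, all succeed in control): 20% − (12% + 20%) = −12 points.
- Best case (the reverse): (20% + 20%) − 12% = +28 points.

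With the loss split 25% / 15%, missing = 0 gives 18.75% v 12.75% (RD +6, OR 1.58). With 15% / 25% it gives 21.25% v 11.25% (RD +10, OR 2.13).

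**6. Partly observed composites.** Table 4 scores an absent postnatal record as 0 and fewer than two vaccination visits as 0. Data collection lets the mother's report stand in for absent record entries. Data management and storage makes nearly all form items compulsory. A woman seen at 3 months should thus usually have every component. A woman lost after baseline usually has only an unfinished ANC count, which is not yet a failure. The group with a definite failure plus a missing component is probably small.

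**The case against.** Analysing women with an observed outcome in the arm of their first registration is common practice, and the ITT sentence allows for exceptions. That is fair as to allocation. But the complete-case sentence covers all analyses, so none remains on the full set.

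A reader might infer that the protocol discards women whose CoC is already known to be 0. It contains no such rule, and the coding and fill-in rules suggest that most women seen at follow-up will have a value. What stands is only that their retention is not stated.

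A reader might also infer that CoC rates are inflated and the effect is biased. The documents do not support that as fact. Unequal loss unrelated to CoC leaves the estimate unchanged, and the same dependence of loss on CoC in both arms leaves the odds ratio unchanged. Rates can be inflated and the effect can be biased; whether they are depends on data not yet seen. The 20% is itself a planning assumption.

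The protocol also acts to limit loss, with detailed contact information and GPS location, and will compare losses by arm. That deserves credit, but it does not correct any bias that remains.

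Finally, where mainly the outcome is missing, a model adjusted for the same baseline predictors does much of what imputation does under missing at random. That is true, so the choice between them is partly preference. Neither addresses data not missing at random, which is why a bounding check is needed.

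**Conclusion.** The point holds in limited form. The protocol names all registered women as the primary population, prescribes an analysis that excludes those with missing data, expects that to be about one fifth, and states no alternative.

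The possible bias is moderate. Under the assumptions shown, a null effect appears as −1.6 to −3.2 points, and a true odds ratio of 1.89 appears as anything from 1.64 to 2.27, against a target of 10 points. These sizes rest on assumed loss splits and CoC rates among the lost. The direction is not predictable from the documents. The silence on partly observed composites is a secondary matter that probably affects few women. The change should be made before the analysis, but nothing here shows that the trial's result will be wrong.

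**What to change.** Replace the sentence that fixes complete case for all analyses. For the primary outcome:

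1. **Scoring.** Set CoC to 0 whenever any observed component is a definite failure, whatever else is missing. An ANC count still running at baseline is not a definite failure.
2. **All registered women.** Prespecify an analysis of the full ITT set by multiple imputation, done separately by arm, respecting municipality clustering and using predictors already collected at baseline (socio-demographic and household data, pregnancy history, first-ANC timing, ANC use to date). Add a check for data not missing at random: missing counted as not complete, or best- and worst-case bounds.
3. **Complete case.** Keep it as one reported analysis.

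The cost is revised wording and modest programming, with no new data collection. The imputation rests on missing at random given the baseline data, and it can do little for women who gave no baseline interview. For them the missing = 0 or bounds check carries the weight.
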